## Sample size and power calculations

In the midline we conduct a village-level survey with the village chief and/or water committee chair in each of the 332 study villages, as well as a household survey from a random sample of 4 households in each village. The objective is to have enough power to estimate initial impact of program implementation, while also helping to finetune the sample size requirements to measure development impacts in the longer-term follow up survey (including generating estimates on the standard deviation and intra-cluster correlation of some of selected health and education measures).

For the midline power calculations, we focus on a primary outcome – whether the household uses an improved water source as their primary source of water. Since the program focuses on villages that have poor water access, we anticipate the level in the control group to be quite low. We also expect a high intra cluster correlation since households in a given village will likely be using the same available water sources as their main water sources.

For these calculations, we limit the risk of Type I errors (false positives) to 5% (alpha = 0.05) and Type II errors (false negatives) to 20% (beta = 0.8). We use the Joint Monitoring Program (JMP)/UNICEF estimate for DRC nationally as an upper bound for improved water access. This is 42%. Since this is a cluster-RCT, we also need to estimate the intra-cluster correlation which is not possible with the available data. Instead we use a conservatively high level of 0.7 given the common infrastructure used in many villages. With 4 households sampled from each village, a 22 percent (or 8-percentage point) increase in access to improved water could be detected using the 121 clusters. Given the large changes anticipated in these operational outcomes, this is expected to be within expectations for the program

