We randomized these into 50 treatment clusters (containing 146 treatment villages) and 71 control clusters (containing 187 control villages). Six villages were randomly dropped to ensure UNICEF target numbers were met, while maintaining treatment and control balance.^[[3]](#footnote-3)^ We stratified randomization to ensure that the treatment and control groups are balanced with respect to their (i) province and (ii) number of villages that make up a cluster. Stratified randomization ensures that the treatment and control groups will be statistically indistinguishable from each other with respect to these characteristics, thereby avoiding bias in treatment effect.

Treatment clusters of villages will receive the status quo VEA intervention, as described above. Control clusters of villages will not receive any intervention from VEA. Data collection procedures will be identical in the two groups, as described below.

Additional discussions were held regarding the possibility of overlaying the school intervention as part of the impact evaluation. Due to the fact that the schools had been pre-selected in each province, this was not possible. There is, however, some possibility that the school intervention is differentially implemented in proximity to treatment and control villages which could threaten the validity of the results, particularly on schooling-related outcomes.

The IE team will work closely with UNICEF and local implementing partners to ensure accurate GPS and implementation tracking information is included in the planned data collection exercises to ensure that, if imbalance in proximity to treatment schools does occur, we will be able to adequately control for this in the analysis.

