# **Estimation**

We will separately estimate the main impacts of VEA on the outcomes listed above, using the following basic specification:

$y_{ihvc}= +\beta_{1}T_{c}+ \boldsymbol{\gamma X}_{ihvc}+\boldsymbol{\delta Z}_{ihvc}\boldsymbol{+}\varepsilon_{i}$ (1)

where $y_{ihvc}$ is the outcome of interest for respondent *i* in household *h* in village *v* in cluster *c* at the follow-up survey, defined above. $T_{i}$ is the treatment indicator that takes value 1 for clusters that were randomly assigned to participate in VEA (“treatment clusters”) and 0 for otherwise (“control clusters”). $\boldsymbol{X}_{ihvc}$ represents a set of strata-specific dummies where strata are based on province and number of villages in the cluster, which will equal 1 if the household falls in that stratum, and 0 otherwise. $\boldsymbol{Z}_{ihvc}$ is a vector of baseline covariates included in the analysis. Specifically we include gender and age (month) dummies for all <5 child health outcomes, but do not include covariates for other outcomes. $\boldsymbol{\gamma}$ and $\boldsymbol{\delta}$ are vectors of associated strata and covariate coefficients respectively. $\varepsilon_{i}$ is an idiosyncratic error term. Our main parameter of interest is $\beta_{1}$, the intention-to-treat effect (ITT). Standard errors will be clustered at the randomization (village cluster) level.

Our primary outcomes comprise four different measures. Our secondary outcomes comprise a broader range of variables, particularly the health behavior outcome set. To reduce the number of statistical tests and reduce the probability of false positives (Type I errors), when an outcome space is comprised of multiple variables (such as the health behavior outcomes) we combine measures into an index following (Kling, Liebman, and Katz 2007). For our four primary outcomes we use the (Benjamini, Krieger, and Yekutieli 2006) method to control the false discovery rate (FDR) and report adjusted p-values for these primary outcome measures. We do not apply this to secondary (exploratory) variables.

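### The 80% power for improved water source belongs to one unadjusted test; under the planned FDR adjustment over four primary outcomes it falls short only if few of them respond

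*Protocol*

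**What the plan says.** The section on sample size and power sizes the midline on one outcome: "we focus on a primary outcome – whether the household uses an improved water source as their primary source of water". Its error rates are "we limit the risk of Type I errors (false positives) to 5% (alpha = 0.05) and Type II errors (false negatives) to 20" per cent, and multiplicity is not mentioned. (The bracketed label in "Type II errors (false negatives) to 20% (beta = 0.8") is a slip: 0.8 is the power, not beta.) The result given is that "a 22 percent (or 8-percentage point) increase in access to improved water could be detected using the 121 clusters".

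The Estimation section names four primary outcomes, of which improved water source is one. For them it uses the two-stage adaptive FDR procedure of 2006, described as a "method to control the false discovery rate (FDR) and report adjusted p-values for these primary outcome measures". It gives no FDR level and does not say whether the adjusted p-value alone decides if a primary hypothesis is supported. The Hypotheses section expects improvement on all four outcomes.

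**The concern.** A power figure is a statement about a particular rejection rule. Here the rule behind the figure is a single test at 0.05. The planned procedure requires a smaller p-value when few of the four outcomes are rejected and can allow a larger one when most are. The stated 20% Type II error therefore does not carry over unchanged.

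Two uses of the midline are affected. The power section argues from this calculation that early programme effects are detectable. The section on key outcomes makes the decision on endline biomarkers depend partly on the midline intermediate measures. If source type improved while time, quantity and sanitation did not, a non-significant adjusted p-value could be read as a well-powered null when it was not one. A partial response is conceivable: the protocol itself describes the record of such interventions as mixed, particularly for sanitation, and gives no power for the other three outcomes.

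**Working it through.** **1. The printed detectable effect.** Inputs from the protocol:
- control rate: "estimate for DRC nationally as an upper bound for improved water access. This is 42" per cent;
- intra-cluster correlation: "Instead we use a conservatively high level of 0.7 given the common infrastructure used in many villages";
- four households per village;
- allocation: "We randomized these into 50 treatment clusters (containing 146 treatment villages) and 71 control clusters (containing 187 control villages").

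This gives 146 × 4 = 584 treatment and 187 × 4 = 748 control households, and 333 × 4 / 121 = 11.0 households per cluster. The design effect is 1 + (11.0 − 1) × 0.7 = 8.0.

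The detectable difference D solves D = 2.802 × √{8.0 × [0.42 × 0.58/748 + (0.42 + D)(0.58 − D)/584]}, where 2.802 = 1.960 + 0.842. The solution is D = 21.3 points.

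Treating the village as the cluster (design effect 1 + 3 × 0.7 = 3.1) gives 13.5 points. At a 42% control rate, only omitting the design effect comes near 8 points (7.7). For a true 8-point effect the standard error is √{8.0 × [0.42 × 0.58/748 + 0.50 × 0.50/584]} = 0.0777, so 0.08/0.0777 = 1.03 and power is about 18% (38% with the village as cluster). The two printed forms also disagree: 8/42 = 19%, and 22% of 42 is 9.2 points.

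The printed figure is not reproduced, so the steps below start from an effect that truly has 80% unadjusted power, whatever its size.

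**2. Threshold when no other outcome is rejected.** Stage 1 of the procedure is a Benjamini–Hochberg step at q/(1 + q). With four tests, a lone rejection needs p ≤ (q/(1 + q))/4.
- q = 0.05: 0.0476/4 = 0.0119, z = 2.515. Power = Φ(2.802 − 2.515) = Φ(0.287) = 61%. Detectable-effect ratio = (2.515 + 0.842)/2.802 = 1.20.
- q = 0.10: 0.0909/4 = 0.0227, z = 2.278. Power = Φ(0.524) = 70%. Ratio = (2.278 + 0.842)/2.802 = 1.11.

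**3. Full two-stage procedure, by simulation.** Four two-sided z-tests. Improved water has noncentrality 2.802, as does every other responding outcome; the rest have none. Stage 2 repeats the step at (q/(1 + q)) × 4/(4 − r), where r is the number rejected at stage 1. The entries are power for improved water, with independent tests first and test correlation 0.6 second.

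| Outcomes responding | q = 0.05 | q = 0.10 |
|---|---|---|
| This one only | about 62% (either) | about 71% (either) |
| Two | 71% to 69% | 81% to 79% |
| Three | 79% to 75% | 88% to 85% |
| All four | 87% to 81% | 94% to 89% |

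The last digit is not firm. A repeat run at correlation 0.6 gave 75.5% for three outcomes at q = 0.05, and 84.4% and 88.5% for three and four at q = 0.10. The first row slightly exceeds step 2 because a false rejection elsewhere occasionally eases the threshold.

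**4. From the protocol's own inputs.** If unadjusted power is the 18% of step 1, adjusted power at q = 0.05 with independent tests is about 7% with one outcome responding and about 8% with two.

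**The case against.** Several points on the other side are sound.

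- **The decision rule is not fully written.** The Estimation section says that adjusted p-values will be reported. It does not fix q or say that they alone decide success. The level of 0.05 is an assumption; at 0.10 the loss with two responding outcomes all but disappears. This stands, and it is why a range is shown.
- **The protocol hypothesises gains on all four outcomes and anticipates large changes.** In that case adjusted power is 81-87% at q = 0.05, so nothing is lost. This stands too.
- **The power section never claims 80% after adjustment.** It limits its error rates to its own calculation. That is fair, and there is no outright contradiction. But the figure is offered without qualification as evidence of detectability, and the document that states it also sets the adjustment.
- **Power under multiplicity could be left to a separate analysis plan.** This carries less weight: the document calls itself the pre-analysis plan and contains both the power statement and the multiplicity rule.
- **Implementation is also judged by other measures.** Functional water points and water committees are secondary outcomes outside the FDR adjustment, so misreading one null is a limited risk.

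A reader might infer that this trial's power for improved water simply is 62% or 71%. The documents do not support that. Those values need q = 0.05, only one or two responding outcomes, and an effect with true 80% unadjusted power, which the printed 8 points does not have on the protocol's inputs.

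**Conclusion.** The point holds in a conditional form and is minor. The stated 80% is the power of an unadjusted test. Under the planned adjustment at q = 0.05 it drops by about 18 points if improved water source alone responds, by 9 to 11 points if one other outcome responds and by 1 to 5 points if three of the four respond. It is kept or exceeded if all four respond. At q = 0.10 there is a clear shortfall, about 9 points, only when this outcome responds alone.

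These figures assume two-sided tests, other responding outcomes of equal strength, correlations between 0 and 0.6, and that the adjusted p-value decides. The detectable effect that fails to reproduce is the larger defect in the same section and has to be settled first; correcting it would leave the present mismatch in place.

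**What to change.** 1. Recompute the detectable effect from the stated control rate, intra-cluster correlation and clusters. Applying the 1.20 multiplier to the printed 8 points would only refine an unsupported number.
2. In the power section, label the power and detectable effect as those of a single unadjusted test.
3. In the Estimation section, state q and that the adjusted p-value is the decision rule for the primary outcomes.
4. Give power or detectable effect under that rule for two cases: only improved water source responds (threshold (q/(1 + q))/4, which is 0.0119 at q = 0.05, with a detectable effect about 1.20 times the unadjusted one), and all four outcomes respond.

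This takes a few lines, with no added sample or data. The cost is a less favourable stated figure in the worst case.

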# **Introduction**

Rural WASH is inadequate in many developing countries, especially those affected by fragility, conflict and violence (FCV), with important implications for human welfare. This is the case in the Democratic Republic of Congo (DRC)— home to approximately 80 million people, including 7% of the world’s extreme poor. Seventy percent of the population is rural, and many residents have experienced protracted instability and violent conflict. The DRC ranked 176^th^ in the Human Development Index in 2015, with a life expectancy of 59.1 years and an adult literacy rate of 77%. The under-5 mortality rate is 104 per 1,000 live births (118 in rural areas). Only 31% of rural Congolese use an improved water source and only 29% use improved sanitation facilities (UNICEF/WHO JMP 2015). 59% of rural households spend more than 30 minutes (on each round trip) to collect drinking water.

Against this backdrop, in 2008, the Government of the DRC launched a national program known as the “National Healthy Village & Schools Programme” (in French, *Villages et Ecoles Assainis-VEA*), a Water and Sanitation (WASH) program financed by DFID and implemented by UNICEF and the Government of DRC’s Ministries of Public Health, and Primary, Secondary, and Professional Education. The VEA’s main objectives are to support improved access to water, hygiene and sanitation (WASH), especially in rural areas. The VEA supports the construction of water and sanitation infrastructure in villages and schools, facilitates local community involvement in management of this infrastructure, conducts behavior change activities, and then formally certifies communities (as “Healthy Villages” or “Healthy Schools”) when they achieve a set of water and sanitation norms. Since 2008, approximately 6,500,000 people in several thousand villages have been reached with WASH services through the program (UNICEF 2017). The program is currently in Phase 2 (2013-2018) which, to support this impact evaluation, will offer an extended VEA programme to an additional 240 villages and 60 schools in 5 provinces (Kongo Central, Kasai, Kasai Central, South Kivu, North Kivu).

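### The stated detectable effect of 8 percentage points is wrong: with the plan's own ICC of 0.7 the midline detects about 21 to 22 points, and power at 8 points is about 18%

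*Protocol*

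**What the plan says.** All inputs but the sidedness of the test are in the protocol.

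- **Error rates** (Sample size and power calculations): "Type I errors (false positives) to 5% (alpha = 0.05") and "Type II errors (false negatives) to 20% (beta = 0.8"). The second is taken to mean 80% power; 0.8 is the power, not beta.
- **Control level** (same section): the protocol takes the JMP/UNICEF "estimate for DRC nationally as an upper bound for improved water access. This is 42" per cent. The Introduction gives a lower rural figure: "Only 31% of rural Congolese use an improved water source".
- **ICC** (same section): "Instead we use a conservatively high level of 0.7 given the common infrastructure used in many villages".
- **Sample**: four households in each village. Treatment and Control Groups gives "50 treatment clusters (containing 146 treatment villages) and 71 control clusters (containing 187 control villages").
- **Conclusion** (same section as the error rates): "a 22 percent (or 8-percentage point) increase in access to improved water could be detected using the 121 clusters". The protocol then judges this to be in line with what the programme should achieve.

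The Estimation section clusters standard errors at the level of the randomized village cluster.

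**The concern.** An ICC of 0.7 is very high, and 121 clusters is a modest number. Together they cannot plausibly give a detectable difference of 8 points on a proportion near 42%. The sentence also gives one effect in two forms that do not match each other at the stated control level.

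This is the protocol's only power statement and its only quantitative support for the midline sample. Main source of drinking water is one of four primary outcomes. A reader who trusts the sentence could take a null midline result as evidence against an 8-point gain, although at the stated ICC the design would miss such a gain about four times in five. Key Outcomes of Interest also makes the decision on endline biomarkers depend partly on the midline intermediate measures, so overstated sensitivity could affect that choice.

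**Working it through.** **Inputs.** Control rate p = 0.42; ICC = 0.7; 4 households per village; 146 treatment villages, so n1 = 146 × 4 = 584; 187 control villages, so n0 = 187 × 4 = 748; 50 + 71 = 121 clusters; mean households per cluster m = 1332/121 = 11.0. The test is assumed two-sided at 5% with 80% power, so the multiplier is 1.96 + 0.84 = 2.80.

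**Formulas.**

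- Design effect: DE = 1 + (m − 1) × ICC
- Standard error: SE = √[p(1 − p) × DE × (1/n1 + 1/n0)]
- Minimum detectable effect: MDE = 2.80 × SE
- Power at 8 points: Φ(0.08/SE − 1.96)

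Here p(1 − p) = 0.42 × 0.58 = 0.2436 and 1/584 + 1/748 = 0.00305.

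**Step 1: try to reproduce 8 points.** With no clustering, DE = 1, SE = √(0.2436 × 0.00305) = 0.0273 and MDE = 7.6 points. Power at 8 points is about 83%. This is the only setting at 42% that comes close to the printed figure.

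**Step 2: apply the stated ICC to the 121 clusters.** DE = 1 + 10.0 × 0.7 = 8.0. SE = √(0.2436 × 8.0 × 0.00305) = 0.0771. MDE = 2.80 × 0.0771 = 21.6 points, which is 51% in relative terms. Power at 8 points is Φ(1.04 − 1.96) = 18%.

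**Step 3: vary the reading.**

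| Reading (p = 42%) | DE | MDE, points | Power at 8 points |
|---|---|---|---|
| ICC 0.7 in the 121 clusters, about 11 households each | 8.0 | 21.6 | 18% |
| Same, only 4 households per cluster (200 vs 284) | 3.1 | 22.5 | about 17% |
| ICC 0.7 within villages only, villages independent | 3.1 | 13.4 | 38% |
| No clustering | 1.0 | 7.6 | about 83% |

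- The choice of variance matters little at 42%: the cluster-level MDE is 21.3 points with unpooled variance and 21.7 to 21.9 with pooled variance.
- Unlimited households per cluster would not help: 2.80 × √[0.2436 × 0.7 × (1/50 + 1/71)] = 21.4 points. The number of clusters is the limit.
- A one-sided test gives about 19 to 20 points.
- With 0.7 within villages and a between-village correlation in the same cluster anywhere from 0 to 0.7, the MDE runs from 13.6 to 21.9 points (pooled variance).
- For an MDE of 8 points at 42%, DE must be (8.0/7.64)² = 1.10, so ICC = 0.10/10.0, or about 0.01.

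**Step 4: vary the control rate.** At the rural 31%, the MDE is 20 to 21 points at cluster level, or 12.6 to 13.1 on the village-only reading. At lower rates the variance must be taken at both arms' rates, because the arms then differ markedly. On that basis the cluster-level MDE is still about 17 points at a 10% control rate and above 12 points at 3%.

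**Step 5: compare the two printed figures.** 0.08/0.42 = 19%. 0.22 × 0.42 = 9.2 points. For 22% and 8 points to agree, the control rate would have to be 0.08/0.22 = 36.4%, a figure the protocol does not give.

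**The case against.** **Level of the ICC.** The protocol motivates the ICC by households in one village sharing a water source, which is village-level reasoning. On that basis the documents support a range of about 13.5 to 22 points. The ambiguity is real and the protocol should resolve it. But the power sentence is framed on the 121 clusters and the standard errors are clustered there, so the upper end is the natural reading. No point in the range is near 8.

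**Control rate.** The 42% is called an upper bound and the protocol expects a low level. A lower rate does reduce the MDE. At ICC 0.7, however, 8 points is reached only if villages are independent and the control rate is about 6%. There an 8-point gain would more than double the rate, which contradicts a 22% increase.

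**Precision of the replacement figure.** The 21.6 points assumes equal cluster sizes. South Kivu has 120 villages in 27 clusters, against 81 in 37 in Kasai Central. Allowing for such differences raises the MDE to about 23 points. Adjustment for strata could lower it, but the protocol gives no figure for that gain. A rerun by the authors with all inputs listed is therefore better than adopting one number from this note.

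**Consequences.** The estimator and its clustered standard errors are unaffected, and the cluster count came from the implementer's village list rather than from this calculation. The protocol anticipates large changes, so a 21-point MDE may still be acceptable. Carry-over to endline sizing is only a risk, since the midline is meant to supply new ICC estimates for selected health and education measures. These points limit the damage but do not make the printed figure right.

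**Conclusion.** The stated detectable effect is wrong. At a 42% control level, ICC 0.7, two-sided 5% alpha and 80% power, the midline detects about 21 to 22 points, more than two and a half times the printed 8, and power at 8 points is about 18%. The most favourable reading of the ICC gives 13 to 14 points and 38%. Separately, 22% and 8 points are not the same effect on a 42% base, whatever power method is used.

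The result assumes a two-sided test, near-equal cluster sizes and no precision gained from strata. None of these could bring the figure to 8 points except a very large gain from strata, which the protocol does not claim. How the error arose is a matter of inference: 8 is close to the unclustered answer, and 22 is close to the correct answer in percentage points, so the units may have been confused.

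**What to change.** In Sample size and power calculations, delete the 22 percent and 8-point figures. State instead that with 121 clusters (50 vs 71), four households per village, a 42% control level and ICC 0.7, the midline detects about 21 to 22 percentage points at 80% power, and that power for 8 points is about 18%. If 0.7 is meant to hold only within villages, say so, give the assumed correlation between villages of the same cluster, and report the matching figure (about 13 to 14 points and 38% power if that correlation is zero). State the sidedness of the test and show the result at the rural 31% as well. Base the claim that the effect is within expectations on the corrected number.

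Two small corrections belong in the same edit: label 0.8 as power rather than beta, and reconcile the 332 study villages with 146 + 187 = 333.

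The cost is one rewritten paragraph and a less favourable stated figure. No change to design, sample or data collection follows from it.
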